### Conceptual Framework

Digital interventions grounded in evidence-informed conceptual frameworks are more likely to be effective than those lacking theoretical design [27]. TransHealthGUIDE is informed by several evidence-based models of suicide prevention and mental health promotion tailored to meet the needs of TGD young adults.

First, the intervention aligns with the Social Ecological Suicide Prevention Model [28], addressing the multiple levels of influence—individual, interpersonal, and structural—that shape TGD individuals’ experiences. Intervention content focuses on helping users navigate and cope with challenges across various contexts, including families, schools, and health care settings, while targeting key drivers of suicidality such as bullying, misgendering, and systemic exclusion.

Second, TransHealthGUIDE draws from the Gender Minority Stress and Resilience Framework [29,30], which emphasizes the impact of societal stigma, discrimination, and oppression on TGD individuals’ mental health [31]. The intervention also emphasizes resilience, using a strengths-based approach to bolster self-efficacy and support-seeking behaviors [32].

Finally, the intervention incorporates an intersectional lens by explicitly addressing intersectionality [33] and centering the experiences of individuals with multiply marginalized and intersecting identities, including those related to race, ethnicity, disability, body size, gender identity, sexual orientation, neurodivergence, and religion. This intersectional framework ensures that the content remains relevant and affirming across a broad spectrum of identities and lived experiences.

### Community Consultations and CAB

In 2022, our team conducted extensive community consultations, engaging with more than 20 key stakeholders to better understand the mental health and support needs of TGD young adults and their families, identify potential intervention strategies, and establish partnerships to support future recruitment and implementation efforts. These consultations included national organizations such as the World Professional Association for Transgender Health (WPATH) and TransLine, as well as local organizations serving TGD young adults and their families within communities across the United States.

In 2023, we formally established a community advisory board (CAB) consisting of 16 members: 7 TGD young adult community members and 9 caregivers and health care providers, including mental health professionals. The CAB is geographically diverse, representing the Northeast, Mid-Atlantic, Midwest, South, and West regions, and 7 (43.8%) of 16 are people of color.

Our CAB has played a central role in guiding the project. Their input has shaped intervention content, informed recruitment and retention strategies, and contributed to the critical decisions regarding implementation of the RCT. Their ongoing engagement ensures the intervention remains grounded in lived experience and community priorities.

### Formative Research

We conducted extensive mixed methods formative research to inform the study design and procedures, intervention content, digital app features and aesthetics, recruitment and retention strategies, and dissemination plans to ensure high acceptability and relevance to our target population.

Between April and August 2022, we conducted 33 qualitative interviews with a purposive sample of 13 medical and mental health care providers, 14 caregivers, and 6 TGD young adults, recruited through community partners and the team’s professional and personal networks. These interviews highlighted a significant unmet need for support and education among both TGD young adults and caregivers, including a desire for accessible, accurate, expert-informed information [34].

In August 2022, we also conducted a one-time survey with 104 young adults, of whom 48 (46.2%) were people of color, recruited via the Prolific.com platform. Eligible participants were US residents aged 18-25 years who identified as TGD. The survey included both closed- and open-ended questions to explore how TGD young adults seek gender- and health-related information online. Findings revealed a high prevalence of depressive distress, with 44 (42.3%) of 104 individuals meeting criteria for clinically elevated symptoms. Low family support was a strong correlate of depressive distress, underscoring the need for interventions aimed at strengthening relationships between TGD young adults and their caregivers [18]. Participants also expressed a strong preference for receiving information through personal stories and lived experiences of other TGD people and families—an insight that directly shaped the narrative and multimedia components of our intervention [35].

Overall, our formative research revealed substantial educational and emotional support needs among TGD young adults and families, particularly regarding navigation of familial and relational dynamics and the search for affirming community connections.

2	Introduction: Caregivers	Caregivers	Caregivers will be able to name and recognize similarities and differences between their experiences and the caregivers highlighted in the video. Caregivers will gain insights from the video about tools they can use in their own parenting or caregiving journey.
3	Terms & Definitions	TGD young adults and caregivers	TGD young adults and caregivers will be able to define foundational sexual orientation, gender identity, and expression (SOGIE) terminology and concepts.
4	Gender Identity	TGD young adults and caregivers	TGD young adults and caregivers will be able to recognize the complexities of gender both in the present and historically; identify and name gender identities under the transgender, nonbinary, and gender expansive identity umbrellas; and foster open and empathetic communication between young people and their caregivers about diverse gender identities.
5	Names	TGD young adults and caregivers	TGD young adults will gain skills in choosing a name (if they have not already) and how to discuss name changes with their caregiver. TGD young adults and caregivers will gain the skills to locate and engage with systems and legal processes to affirm and legalize names for TGD young adults.
6	Pronouns	TGD young adults	TGD young adults will gain the skills to effectively communicate their pronouns and leverage support in settings such as home or school.
7	Gender Expression	TGD young adults and caregivers	TGD young adults and caregivers will recognize the complexities of gender expression and gain skills to respectfully engage with people outside of gender assumptions based on appearance. TGD young adults will name and recognize similarities and differences between their experiences of and desires for gender expression and those in the videos.
8	Imagining My Future	TGD young adults	TGD young adults will build a foundation of skills to foster self-compassion and care when facing challenging situations. TGD young adults will develop goal-setting skills and write gender- and relationship-related goals for the next 3 months.
9	Goals: Self & Youth	Caregivers	Caregivers will build a foundation of skills to foster self-compassion and generate a circle of support for themselves and their young person. They will define and write goals for their own growth and around engaging positively and affirmatively with their young person.
10	Dysphoria	TGD young adults	TGD young adults will gain skills to recognize and address dysphoria, as well as access support.
11	What to Expect/Transitions	TGD young adults	TGD young adults will be able to relate to the experiences shared by TGD individuals in various stages, identify key elements of psychological and social transition, and gain insights into the personal psychological benefits of the transition process.
12	Intersectionality: Identities, Communities, and Me	TGD young adults and caregivers	TGD young adults and caregivers will be able to describe intersectionality and how different identities have different levels of marginalization in society. TGD young adults and caregivers will be able to describe how stigma and discrimination impact TGD people, especially those with multiple, marginalized identities.
13	Communicating with Caregivers	TGD young adults	TGD young people will gain skills to communicate effectively, establish boundaries, and improve their relationships with their caregivers.
14	Communicating with Your TGD Loved One	Caregivers	Caregivers will gain skills to facilitate improved communication with their young person, including how to handle mistakes, begin again, and build healthy relationships with their young person.
15	Struggling to Accept	Caregivers	Caregivers will gain skills to acknowledge and appropriately process their own emotions, such as grief, confusion, and anger, without burdening their young person. They will also gain insights on how to provide support to their young person, even when struggling to accept or understand their gender identity.
16	Misgendering	TGD young adults	TGD young adults will acquire coping skills and stress management techniques to enhance their mental health and well-being when facing misgendering and other forms of transphobia.
17	Coming Out	TGD young adults	TGD young adults will develop a plan for coming out, prioritizing their safety and personal desire for privacy.
18	Navigating Coming Out	Caregivers	Caregivers will gain consent-based tools to effectively communicate about their young person’s gender with close friends and extended family members, while respecting their young person’s consent.
19	Setting Health Boundaries	TGD young adults	TGD young adults will assess and acquire healthy relationship tools and boundary skills to ensure their safety and emotional well-being while potentially being treated differently.
20	Privacy & Confidentiality	Caregivers	Caregivers will be able to summarize the complexities of confidentiality and consent-based parenting that centers on their TGD young adult.
21	Healthy Peer Relationships	TGD young adults	TGD young adults will learn foundational tools for building healthy and safe relationships, including intimate, platonic, sexual, and romantic relationships. They will also gain the skills to assess their needs and activate a safety plan, including local and national resources for preventing and addressing potential harm or violence.
22	The Talk: Trans Edition	Caregivers	Caregivers will gain skills to effectively discuss sexual health, sexual orientation, and gender identity with their TGD young adult. Caregivers will be able to locate local and national resources to facilitate accurate and safe conversations about dating and sexual health topics with their young person.
23	Managing Self-Harm	TGD young adults	TGD young adults will be able to identify self-harm behaviors and triggers; will develop skills to redirect and seek help from appropriate avenues and resources; and will be able to recognize suicidal ideation and behaviors in themselves and others, when and how to seek help, and learn about appropriate resources to respond to suicidality.
24	Finding Support	Caregivers	Caregivers will build a foundation of skills to foster self-compassion and generate a circle of support for themselves and their young person. They will also gain tools related to self-harm prevention and treatment for their young person.
25	Mental Health Treatment	TGD young adults and caregivers	TGD young adults and their caregivers will recognize ways to find and access mental health care providers who meet their unique needs.
26	Talking with Providers	TGD young adults and caregivers	TGD young adults and their caregivers will learn how to interact with health care providers when seeking regular care.
27	Insurance 101	TGD young adults and caregivers	TGD young adults and their caregivers will learn how to research and navigate insurance systems.
28	Social Transition in Educational Institutions	TGD young adults and caregivers	TGD young adults and caregivers will identify best practices for creating supportive environments at educational institutions and developing gender transition plans.
29	Addressing Bullying & Discrimination	TGD young adults and caregivers	TDG young adults and their caregivers will be prepared to address bullying and harassment in educational institutions and other environments, including cyberbullying, through a law and policy lens.
30	Gender at Work	TGD young adults	TGD young adults will locate resources grounded in law & policy to build their skills in self-advocacy and protection of their rights at work.
31	Addressing Homelessness	Caregivers	Caregivers will identify and name resources available to TGD young adults who face family rejection and will gain the skills to name protective parenting practices to prevent these outcomes.
32	Homelessness	TGD young adults	TGD young adults will identify and name resources available to them when facing family rejection and will gain the skills to create a safety plan with affirming, trustworthy adults in their lives.
33	Looking Ahead	TGD young adults and caregivers	TGD young adults and their caregivers will reflect on their experiences within the app and what they have learned, and set new goals for their continuing journey.

^a^TransHealthGUIDE: Transforming Mental Health for Transgender and Gender-Diverse Young Adults Using Interventions to Drive Equity.

^b^TGD: transgender, nonbinary, and gender diverse.

Additional features of the app include: a goal-setting tool to promote self-efficacy and track progress, a community resources hub offering curated local and national supports, and moderated Q&A forums with TGD community members and expert contributors across various areas of TGD health.

### Study Population and Inclusion and Exclusion Criteria

Two participant groups are being enrolled in the study: (1) TGD young adults ages 18-24 years and (2) adult caregivers of TGD young adults who are enrolled in the study. Inclusion and exclusion criteria for both groups are detailed in Table 2.

**Table 2 table2:** Inclusion and exclusion criteria for TGD^a^ young adults and caregivers in TransHealthGUIDE^b^.

Participant group			Inclusion criteria		Exclusion criteria
**TGD young adults**					
	1	Ages between 18 and 24 years (inclusive)		Ages under 18 years or over 24 years	
	2	A person of TGD experience (transgender, nonbinary, gender diverse, or not cisgender)		Not a person of TGD experience (ie, cisgender)	
	3	Resides in one of the following locations: California, Connecticut, Illinois, Maryland, Massachusetts, New Jersey, New York, Oregon, Vermont, and Washington, DC		Does not reside in the 10 specified locations	
	4	Able to read, write, and communicate in English		Not able to read, write, or communicate in English	
	5	Has access to a smartphone/device or computer with internet connectivity		Does not have access to a smartphone/device or computer with internet connectivity	
	6	Provides informed consent to participate		Does not provide informed consent to participate	
**Caregivers**					
	1	Ages 18 years or older		Ages under 18 years	
	2	A parent or legal guardian of the TGD young adult during their minority		Not a parent or legal guardian of the TGD young adult	
	3	Has a TGD young adult aged 18-24 years enrolled in the study		Does not have a TGD young adult in the study	
	4	Resides in one of the following locations: California, Connecticut, Illinois, Maryland, Massachusetts, New Jersey, New York, Oregon, Vermont, and Washington, DC		Does not reside in the 10 specified locations	
	5	Able to read, write, and communicate in English		Not able to read, write, or communicate in English	
	6	Has access to a smartphone/device or computer with internet connectivity		Does not have access to a smartphone/device or computer with internet connectivity	
	7	Provides informed consent to participate		Does not provide informed consent to participate	

^a^TGD: transgender, nonbinary, and gender diverse.

^b^TransHealthGUIDE: Transforming Mental Health for Transgender and Gender-Diverse Young Adults Using Interventions to Drive Equity.

We aim to recruit 500 participants overall, including 375 TGD young adult participants across 10 US states (listed alphabetically): California, Connecticut, Illinois, Maryland, Massachusetts, New Jersey, New York, Oregon, Vermont, and Washington, DC. Our recruitment goals include at least 50% (250 of 500 participants) identifying as people of color and at least 125 caregivers, resulting in 125 TGD young adult-caregiver pairs.

To maintain the dyadic framework of the intervention, caregivers may only participate if their corresponding TGD young adult is already enrolled. Each TGD young adult is asked to identify a primary caregiver to invite into the study, but young adults can participate in the study without a caregiver.

Caregivers must reside in one of the 10 study states due to legislative and logistical considerations. These locations were selected in consultation with experts that helped identify supportive jurisdictions for TGD young adults, ensuring a foundation of safety and feasibility for the intervention.

For TGD young adults attending college, eligibility is based on their current state of residence during the study period, not their permanent home address. TGD young adults and their caregivers can reside in different states, as long as each lives in one of the 10 eligible states.

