**Methods:**

From 2021 to 2024, a multidisciplinary team of academic and community partners conducted formative research and codeveloped a digital app containing 33 self-paced modules, communication, and interactive resources. The content is grounded in the Social Ecological Suicide Prevention Model and the Gender Minority Stress and Resilience Framework, designed to enhance family support and community connection for TGD young adults and their families. TGD young adults (ages 18-24 years) and their caregivers are prospectively enrolled and randomized in 10 US states (California, Connecticut, Illinois, Maryland, Massachusetts, New Jersey, New York, Oregon, Vermont, and Washington, DC). Participants complete self-reported surveys at baseline, 6 months, and 12 months, assessing sociodemographics, family support, community connection, suicidal ideation, depressive distress, and intervention acceptability. App usage and engagement are tracked via metadata. The target sample size is 500 TGD young adults, with 50% (n=250) identifying as people of color and 125 TGD young adult-caregiver dyads.

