### Study Objective and Aims

This prospective randomized controlled trial (RCT) evaluates the effectiveness of an educational and supportive app-based digital intervention in reducing suicidal ideation and depressive distress among TGD young adults across 10 US states. TransHealthGUIDE (Transforming Mental Health for Transgender and Gender-Diverse Young Adults Using Interventions to Drive Equity) is a co-designed digital app developed in partnership with TGD communities. The intervention engages, empowers, and fosters connections between TGD young adults and their families.

The primary aim of this study is to test the effectiveness of a digital app-based intervention in reducing past 3-month suicidal ideation and past 2-week depressive distress among TGD young adults and their caregivers, by comparing participants randomized 1:1 to an immediate intervention arm versus a 6-month deferred intervention arm (waitlist control).

The secondary aims are (1) to assess the impact of the intervention on family functioning (past 3-month family communication, satisfaction, and acceptance) and on community belonging and connection for TGD young adults and their caregivers, and (2) to examine the dyadic relationship dynamics between TGD young adults and their caregivers participating in the intervention.

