**Figure 1 figure1:**
[figure not shown]
TransHealthGUIDE (Transforming Mental Health for Transgender and Gender-Diverse Young Adults Using Interventions to Drive Equity) study schema. Target sample size is 500 TGD young adults, with one-quarter (125 participants) in a dyad with a caregiver (target sample size of 125 caregivers). TGD: transgender, nonbinary, and gender diverse.

Participants in the immediate intervention arm receive full access to the TransHealthGUIDE digital app for the first 6 months. This is followed by a 6-month observation period during which they retain access to the app but receive no new intervention content or engagement prompts. Participants in the deferred intervention arm receive limited access to the app for the first 6 months, consisting primarily of curated local, regional, and national support resources. At the 6-month mark, participants in the deferred arm are granted full access to the digital app for the remainder of their participation.

Survey assessments are administered at baseline, 6 months, and 12 months to evaluate primary outcomes (past 3-month suicidal ideation and past 2-week depressive distress) as well as secondary measures.

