### Intervention Delivery

TGD young adults and caregivers assigned to the immediate intervention arm receive full access to the digital app. After informed consent is obtained, participants are emailed a personalized link to download the app and complete registration. Only enrolled participants are able to create an account and access the app content. Participants randomized to the deferred arm also receive immediate access to the app; however, they are initially limited to viewing the Community Resources tab, which includes local, regional, and national resources. All other features are automatically unlocked after 6 months.

The intervention supports dyadic participation, with approximately one-third of TGD young adults expected to participate alongside a caregiver. With mutual consent, TGD young adults and caregivers may choose to link their accounts. All linking is reviewed and performed manually by study staff to ensure participant privacy and data integrity.

For dyads, accounts are manually linked by research staff once both participants have downloaded the app and completed registration. If linking is requested after enrollment, the app includes a feature that allows both participants to independently provide consent for linking. Once consent is confirmed, the study team is notified, and accounts are linked manually. Linking allows for shared activities and progress tracking but is entirely optional. Participants may request to unlink their accounts at any time, and study staff will promptly honor the request. This option, along with the voluntary nature of linking, is clearly communicated during the consent process and outlined in study documentation.

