### Statistical Analysis

#### Power

The study aims to enroll 500 TGD participants between the ages of 18 and 24 years, 125 caregivers, and one-quarter of the young adult sample in a TGD young adult-caregiver dyad. The primary outcome of interest is past 3-month suicidal ideation.

Power calculations determined the sample size needed to detect a significant difference in suicidal ideation between the immediate and deferred intervention arms. To detect an effect size of at least 30% (risk ratio=0.70) in the reduction of suicidal ideation from baseline to 6 months postrandomization, a total sample size of 400 participants (200 per arm) is required to achieve 80% power at a 0.05 significance level.

We selected a 30% effect size threshold based on the assumption that smaller differences would not be clinically meaningful for public health scale-up. To account for an estimated 20% attrition rate, we plan to enroll 500 TGD young adult participants and 125 caregivers at baseline, yielding an anticipated analyzable sample of 400 TGD young adult participants and 100 caregivers.

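### The young-adult recruitment target is 375 in one section and 500 in three others; recruiting only 375 would cut the stated 80% power to about 68%.

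*Protocol article*

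**What the plan says.** The places that give the size or make-up of the sample fall into two groups.

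**Sections that point to 375 young adults**
- Study Population and Inclusion and Exclusion Criteria, text below Table 2: "We aim to recruit 500 participants overall, including 375 TGD young adult participants across 10 US states". The same paragraph asks for at least 125 caregivers and sets the people-of-color goal at 250 of 500 participants.
- Intervention Delivery: "approximately one-third of TGD young adults expected to participate alongside a caregiver".

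**Sections that point to 500 young adults**
- Abstract, Methods: "The target sample size is 500 TGD young adults, with 50% (n=250) identifying as people of color and 125 TGD young adult-caregiver dyads".
- Figure 1 legend: "Target sample size is 500 TGD young adults, with one-quarter (125 participants) in a dyad with a caregiver", with a target of 125 caregivers.
- Statistical Analysis, Power: "To account for an estimated 20% attrition rate, we plan to enroll 500 TGD young adult participants and 125 caregivers at baseline". This section requires 400 analysable (200 per arm) for 80% power at the 0.05 level to detect a risk ratio of 0.70. It expects 400 young adults and 100 caregivers to be analysable, and it puts one-quarter of the young adults in dyads.

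The primary aim, under Study Objective and Aims, speaks of effects on suicidal ideation and "past 2-week depressive distress among TGD young adults and their caregivers", whereas the sample size is built on young adults.

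**The concern.** The two groups cannot both be right. In the first, 500 is the total head count with caregivers included. In the second, 500 is the number of young adults alone and caregivers come on top. The difference is 125 young adults, a quarter of the powered sample.

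The paragraph containing 375 is the one that sets out recruitment goals, so a team could reasonably recruit to it. If it did, the primary comparison of suicidal ideation would have fewer young adults than the Power section says are needed. The effect at stake is also the smallest one the sponsor regards as worth scaling up.

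**Working it through.** **Inputs**
- Analysable number required: 400 young adults, 200 per arm (Power).
- Power 80%, significance level 0.05, risk ratio 0.70 (Power). Sidedness is not stated. Two-sided is assumed here because the primary analysis uses Wald tests with 95% confidence intervals.
- Allocation 1:1 (Intervention Allocation and Randomization).
- Attrition 20% (Power).
- Young-adult target: 500 (Abstract, Figure 1 legend, Power) or 375 (Study Population).
- Control-arm risk of ideation: not stated in the article. The main check below does not need it.

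**Step 1. Reproduce the plan's own figures.**
400 / (1 − 0.20) = 500 young adults, and 125 × 0.80 = 100 caregivers. Both match the Power section.

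**Step 2. Test each target for internal consistency.**
- 375 + 125 = 500 people, and 125 / 375 = 33.3%. This matches the 500 overall in Study Population and the one-third in Intervention Delivery.
- 500 + 125 = 625 people, and 125 / 500 = 25%. This matches the one-quarter in the Figure 1 legend and in Power. The total of 625 is my sum and is not printed in the article.

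Each set adds up by itself, so the problem is a conflict between sections and not a slip of arithmetic within one.

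**Step 3. Apply the plan's attrition to 375.**
375 × 0.80 = 300 analysable, or 150 per arm. That is 100 fewer than the 400 required.

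**Step 4. Power at 150 per arm.**
Take the plan's 80% at 200 per arm as given. The standardised effect is then 1.960 + 0.842 = 2.802, and it shrinks with the square root of the sample size:

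Power = Φ(2.802 × √(300/400) − 1.960) = Φ(2.802 × 0.866 − 1.960) = Φ(0.467) ≈ 0.68.

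**Step 5. Check that the result does not hang on the formula.**
For each version of the two-group test, the control risk was set so that 200 per arm gives exactly 80%, and power was then recomputed at 150 per arm:

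| Version | Power at 150 per arm |
|---|---|
| Pooled two-proportion | 67.9% |
| Unpooled | 67.9% |
| Wald test on the log risk ratio | 67.9% |
| Continuity-corrected | 66.8% |
| One-sided test | 69.4% |

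**Step 6. Sensitivity to attrition.**
If all 375 were analysed with no losses, power would be Φ(2.802 × √(375/400) − 1.960) ≈ 0.77. Even then the plan's 80% is not reached.

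**The case against.** The best defence is that this is a drafting slip. The Abstract, the Figure 1 legend and the Power section agree on 500 young adults, and the Power section is exact. The 375 may be 500 − 125, that is, the young adults expected to take part without a caregiver. On that reading the 500 overall are all young adults, and the people-of-color goal of 250 out of 500 is the same as in the Abstract. The one-third in Intervention Delivery is only an approximate expectation.

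Part of this stands. A slip is at least as likely as a second design, and nothing shows that the team is recruiting to 375. The power loss is therefore conditional. But the sentence does not describe the 375 as young adults without caregivers. It gives them as the young-adult part of 500 participants, and the rescue reading leaves the one-third unexplained. Nothing in the article resolves the conflict, and the condensed format of an article does not account for two different targets.

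Two stronger readings are tempting and should not be drawn:
- A reader might infer from the primary-aim wording that the required 400 could include caregivers. The Power section rules this out: it says that the analysable 400 are young adults and counts 100 caregivers separately.
- A reader might solve backwards for the control risk (about 45% under a simple two-sided two-proportion test) and treat it as the sponsor's assumption. It is not in the article, it changes with the method and sidedness assumed, and an article may leave it to the full protocol. How power varies with that risk is also a different question from 375 versus 500.

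**Conclusion.** The contradiction is real and unresolved. Study Population (375 young adults within 500 participants) and Intervention Delivery (about one-third in dyads) conflict with the Abstract, the Figure 1 legend and the Power section (500 young adults, with the last two adding 125 caregivers and a one-quarter dyad share). The people-of-color goal inherits the same ambiguity in its denominator, though this does not touch the primary analysis.

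The 80% power claim is consistent with 500 young adults and is not challenged here. It would not hold at 375: power would be about 68%, close to a one-in-three chance of missing a true risk ratio of 0.70. That figure rests on three assumptions: the plan's 20% attrition applies equally to the 375, the test is two-sided at 0.05, and the plan's 80% at 200 per arm is correct. Given the last of these, the result hardly depends on the control risk.

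This needs correction because the sample size is a figure the trial relies on.

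**What to change.** - In Study Population, state the powered design: 500 young adults plus 125 caregivers. Give the 250 people-of-color goal the same denominator as in the Abstract, the 500 young adults.
- In Intervention Delivery, change the expected dyad share to one-quarter.
- In Study Objective and Aims, align the primary-aim wording with the young-adult population on which the Power section is built.
- If 375 is in fact the intended target, leave Study Population as it is. Instead restate the Power section as 300 analysable after 20% attrition with about 68% power for a risk ratio of 0.70, and bring the Abstract and the Figure 1 legend into line.

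The first course is a text correction plus a check that the working recruitment targets match. It adds nobody beyond the powered design. Five young adults had been enrolled by May 2, 2025, so at that date the target could still be set straight without loss.
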